#### Eligibility

Eligible participants will be women (including both cisgender and transgender) aged 18 to 45 years (inclusive) who present with moderate depressive symptoms at baseline, defined as a score of 17 to 23 on the 17-item Hamilton Depression Rating Scale (HDRS-17). Additional inclusion criteria are fluency in Catalan or Spanish, regular internet access, and the ability to independently use a digital device (eg, smartphone, tablet, or computer).

Participants will be excluded if they are currently receiving psychological therapy, as concurrent structured psychotherapy would confound the estimation of the 3D Program’s effect; have participated in another interventional clinical trial for depression in the past 3 months; are pregnant or planning to become pregnant during the study period, given the distinctiveness of perinatal depression and because pregnancy-related hormonal fluctuations would confound the exploratory biomarker analyses; have cognitive impairment that would interfere with informed consent or study participation; or currently present with psychotic symptoms, active suicidal ideation, or substance use disorder. Women older than 45 years will be excluded to minimize potential confounding effects of perimenopausal hormonal changes. Participants with severe depression will be excluded due to safety considerations, as this population requires more intensive, closely monitored treatment than the 3D Program is designed to provide.

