### Data Analysis

#### Sample Size Calculation

A total sample size of 120 participants (60 per group) is required. This estimation was calculated based on a design with 2 groups and 3 measurement points. Assuming an effect size of *f* of 0.15, a significance level of *α* of .05, and a power of 0.90, with a correlation among repeated measures of 0.5 and assumed sphericity (*ε*=1), the minimum sample size estimated was at 96 patients. This number was increased to 120 to account for an anticipated 20% attrition rate. The sample size was determined using G*Power version 3.1.7.

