#### Outcome Analysis and Longitudinal Modeling

Primary and secondary outcomes will be analyzed using an intention-to-treat (ITT) approach, with all participants analyzed according to their original randomization group. Linear mixed-effects models (LMMs) will be used to examine changes over time and between groups for the HDRS-17, WHODAS 2.0, EQ-5D-5L, PSS, and MEDI-Q scores. These models will include fixed effects for group, time, and their interaction, with a random intercept for participants to account for within-subject correlation over time.

While change scores may be calculated for descriptive or interpretative purposes, the LMMs will serve as the primary inferential approach. In the event of a significant group × time interaction, post hoc simple effect analyses will be conducted to evaluate between-group differences at a specific time point and within-group changes from baseline, using estimated marginal means with appropriate corrections for multiple comparisons.

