#### Missing Data

Following the ITT principle, LMMs will be applied without imputation, as they appropriately handle missing data under the missing at random assumption, and imputation may introduce unnecessary bias. Cluster and factor analyses will also be conducted without imputation, as they rely solely on baseline data, assuming that missingness is minimal and not systematic. Multiple imputation will be performed only for analyses that require it, such as multiple regression models and partial least squares regression.

All analyses will be 2-tailed, with statistical significance set at *P*<.05.

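### The random-intercept model implies equal HDRS-17 variance at all visits, but eligibility compresses baseline; intervals for the 12- and 26-week group differences are likely too narrow

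*Protocol article*

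**What the plan says.** Under Outcome Analysis and Longitudinal Modeling, the article sets linear mixed models for HDRS-17 and the secondary scales, with fixed effects for group, time and their interaction, "with a random intercept for participants to account for within-subject correlation over time". No random slope, visit-specific residual variance or unstructured covariance is named. The group × time interaction is tested first. If it is significant, between-group differences at particular visits and within-group changes are estimated from marginal means, with a multiplicity correction that is not named.

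Under Eligibility, moderate symptoms at baseline are "defined as a score of 17 to 23 on the 17-item Hamilton Depression Rating Scale (HDRS-17". Under Primary Outcome Measures, the outcome is change in HDRS-17 from baseline to 12 weeks (T1) and 26 weeks (T2), on a scale stated to run from 0 to 52.

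The Sample Size Calculation uses "a design with 2 groups and 3 measurement points", an "effect size of *f* of 0.15", "a significance level of *α* of .05", "a power of 0.90", a common correlation of 0.5 and sphericity. Under Missing Data, "All analyses will be 2-tailed".

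**The concern.** A random intercept with one residual variance gives T0, T1 and T2 the same variance and every pair of visits the same correlation. The trial's own entry rule makes equal variance unlikely for HDRS-17. Baseline is confined to seven adjacent scores, whereas at T1 and T2 some women will have remitted and others will not. The fitted model then averages a small baseline variance into the variance it uses at follow-up. A group difference at T1 or T2 gets too small a standard error whenever the true variance at that visit exceeds the three-visit average.

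Those visit-specific differences, with their intervals, are the figures most likely to be quoted as the 12- and 26-week effect.

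**Working it through.** **The plan's own figure.** For the within-between interaction in repeated-measures ANOVA, λ = f²·N·m/(1−ρ), with df1 = 2 and df2 = (N−2)·2. With f = 0.15, m = 3, ρ = 0.5 and N = 96, λ = 0.0225 × 96 × 3 / 0.5 = 12.96 and df2 = 188. Power is 0.902; at N = 94 it is 0.896. So 96 is the smallest even total, and 96/(1−0.20) = 120. The sample size reproduces exactly.

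**Inputs for the variance check.**
- Baseline SD, from Eligibility: at most (23−17)/2 = 3, and 2.0 if scores are uniform on 17-23.
- Follow-up SD: not in the article. Assumed 4-7.
- Correlations: no visit-specific values in the article. Assumed mainly 0.3 (baseline with follow-up) and 0.6 (T1 with T2).

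**Differences at a visit (complete data).** Model SE / true SE = √(mean of the three variances / variance at that visit). The true two-sided error of a nominal 5% test is 2·[1 − Φ(1.96 × ratio)]. This ratio does not depend on the correlations.

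| SD at T0/T1/T2 | Mean variance | Ratio at T1 | Ratio at T2 | True error at T2 |
|---|---|---|---|---|
| 2/4/4 | (4+16+16)/3 = 12.0 | 0.866 | 0.866 | 9.0% |
| 2/6/6 | (4+36+36)/3 = 25.3 | 0.839 | 0.839 | 10.0% |
| 3/6/6 | (9+36+36)/3 = 27.0 | 0.866 | 0.866 | 9.0% |
| 2/6/7 | (4+36+49)/3 = 29.7 | 0.908 | 0.778 | 12.7% |
| 3/4/4 | (9+16+16)/3 = 13.7 | 0.924 | 0.924 | 7.0% |
| 3/3/3 | 9.0 | 1.000 | 1.000 | 5.0% |

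Simulation agrees. With 48 per arm, the ratio at T2 was 0.79-0.95 and ungated rejection 6.5-12.5%. With 60 per arm, 20% dropout by T2 and follow-up SDs of 4-8, the ratio at T1 and T2 was 0.78-0.89 and rejection 8-13%. Coverage of nominal 95% intervals at T2 was 91% (2/4/4), 90% (2/6/6), 91% (3/6/6) and 88% (2/6/7). When equal variances and correlations were simulated, the ratios were 0.99-1.02 and rejection about 5%.

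**Differences in change from baseline.** The ratio becomes √(mean of the three pairwise difference variances / that difference variance). For SDs 2/6/6 with correlations 0.3 and 0.6:
- Var(T1−T0) = Var(T2−T0) = 4 + 36 − 2(0.3)(12) = 32.8.
- Var(T2−T1) = 72 − 2(0.6)(36) = 28.8.
- The mean is 31.47, so the ratio is √(31.47/32.8) = 0.979 and the true error 5.5%.

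With all correlations 0.5, the three variances are 28, 28 and 36, and the ratio is √(30.67/28) = 1.047 (error 4.0%). Over the assumed range it runs from 0.88 to 1.15. Simulated rejection with dropout was 4.2-7.6%.

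**The gate.** The interaction test rejected 4.7-5.5% of the time with complete data and 5.3-6.4% with dropout. Under a global null, a false T1 or T2 difference got through the gate in 2.5-4.7% of trials, before any multiplicity correction.

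**Effect at T1 only.** The true T1 effect opens the gate, so the gate no longer protects the T2 test. False T2 claims at an uncorrected 5% occurred in 8.9% (2/4/4), 9.5% (2/6/6), 8.2% (3/6/6) and 12.2% (2/6/7) of trials. With Bonferroni over two visits the rate was about 4-8% against a nominal 2.5%. At 3/4/4 the uncorrected rate cannot exceed the ungated 7.0%.

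**The case against.** The strongest reply is that the planned procedure is not an ungated 5% test at each visit. Visit-specific contrasts follow only a significant interaction and carry a multiplicity correction. The interaction holds its level, and under a global null the whole procedure makes few false claims. All of this stands. A reader might infer that the primary test is invalid or that the trial's type I error is 8-13%. The documents do not support that: those rates belong to ungated, uncorrected visit contrasts. A reader might also infer that every standard error is too small. For change from baseline, which is the stated primary outcome, the error is modest and can go either way.

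Second, the article names a random intercept but does not call it the only term, and it refers to an analysis plan that may set a heterogeneous residual structure. That is possible. But the article does not leave the point open: it names the device for within-subject correlation, and that device alone does not fit this outcome. The assumption of "and a power of 0.90, with a correlation among repeated measures of 0.5 and assumed sphericity" belongs to the sample-size calculation and does not settle the analysis covariance.

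Third, the size depends on follow-up SDs that the article does not give. This also stands.

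The gate and the correction leave two things unrepaired. Gating does not widen an interval computed from the wrong variance. And the correction only lowers the nominal level: with Bonferroni over two visits, the T2 error is still above its 2.5% target when the effect is at T1 only.

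**Conclusion.** The concern holds in limited form. As written, the model implies equal HDRS-17 variance at the three visits, and the entry criterion works against this. With baseline SD 2-3 and an assumed follow-up SD of 4-7, model standard errors for the between-group differences at 12 and 26 weeks are roughly 5-22% too small, and 95% intervals cover about 88-94%. If the effect is at 12 weeks only, a false 26-week difference is declared in about 8-12% of trials uncorrected in most of the scenarios examined, or about 4-8% against 2.5% with Bonferroni over two visits.

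The interaction test and the sample size are not in question. If the follow-up SD is only about 3, with baseline at its maximum of 3, the problem vanishes. Severity is moderate: it should be fixed, but it does not overturn the primary inference.

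**What to change.** For HDRS-17, replace the random-intercept covariance with an unstructured covariance across visits (SPSS MIXED, REPEATED with COVTYPE(UN)). There are two ways to do this:

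- **Preferred:** model T1 and T2 as the responses, with group, visit, group × visit, baseline HDRS-17 and baseline × visit. In simulation, baseline adjustment held the error of the visit differences at 4.2-5.7%. Group × visit in this model tests only whether the effect differs between T1 and T2, so the gate must be restated as a joint test of the two group differences.
- **Alternative:** keep T0 as a response with unstructured covariance and a common baseline mean for the two arms. Women with a baseline score only then stay in the model.

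Name the multiplicity correction at the same time.

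The cost is small. The random intercept uses 2 covariance parameters; an unstructured matrix uses 3 for two visits or 6 for three. The data and software are unchanged. The article reports 8 women enrolled as of April 2026 and no analysis begun, so the change can be recorded as an amendment before any outcome data are analysed.

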**Methods:**

A total of 120 women presenting with moderate depressive symptoms (17-item Hamilton Depression Rating Scale score 17‐23), aged 18 to 45 years, will be randomized to receive either the 10-week 3D Program or informational video content, with both groups continuing treatment as usual. The 3D Program will integrate personalized therapist support, self-guided digital modules, and a moderated online group, with content cocreated alongside women with lived experience of depressive symptoms. The primary outcome will be the change in depressive symptom severity, measured by the 17-item Hamilton Depression Rating Scale at 12- and 26-week postbaseline assessments. Secondary outcomes will include functioning, quality of life, perceived stress, and menstrual-related distress. Additionally, the study will explore potential biological predictors of treatment response, analyzing metabolic markers related to tryptophan metabolism and adrenal steroid pathways across multiple biological matrices. Data analyses will use linear mixed-effects models and multivariate techniques to examine treatment effects and possible biomarker associations.

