To address persistent gaps in accessible, personalized, and gender-sensitive mental health care, this study will conduct a randomized controlled trial (RCT) evaluating the efficacy of the 3D Program, a gender-sensitive, guided iCBT intervention for women with moderate depressive symptoms, which was cocreated with multidisciplinary experts and women with lived experiences. We hypothesize that participants receiving the 3D Program will experience greater reductions in depressive symptoms compared to controls. Additionally, we will explore metabolic biomarkers related to tryptophan and steroid pathways in relation to treatment response.

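### The stated 90% power belongs to the group × time interaction, while benefit at 12 or 26 weeks is tested behind that interaction, with correction and without baseline adjustment, at lower power

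*Protocol article*

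**What the plan says.** The Introduction states a directional hypothesis: "participants receiving the 3D Program will experience greater reductions in depressive symptoms compared to controls". The Abstract gives the primary outcome as change in symptom severity "measured by the 17-item Hamilton Depression Rating Scale at 12- and 26-week postbaseline assessments", and Primary Outcome Measures repeats both visits. Neither visit is named as the one that decides the trial.

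Sample Size Calculation says "This estimation was calculated based on a design with 2 groups and 3 measurement points", with "Assuming an effect size of *f* of 0.15", "a significance level of *α* of .05" and "a power of 0.90", a correlation of 0.5 among repeated measures and sphericity. The result is 96, raised to 120 for 20% attrition.

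Outcome Analysis and Longitudinal Modeling makes a linear mixed model the primary inferential approach. Its fixed effects are group, time and their interaction, with a random intercept. Baseline HDRS-17 enters as one of the three responses and not as a covariate. Comparisons at a single visit are conditional: "In the event of a significant group × time interaction, post hoc simple effect analyses will be conducted to evaluate between-group differences". They use estimated marginal means and a correction whose method is not named. The Missing Data section adds "All analyses will be 2-tailed".

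**The concern.** The conclusion a reader wants is that women given the 3D Program have lower HDRS-17 scores than controls at 12 weeks, at 26 weeks, or at both. As written, that statement is available only after two hurdles: a non-directional 2-df test over three visits, then a corrected comparison at one visit. One of the three visits is baseline, where randomisation makes the groups equal in expectation. The visit-specific comparison takes the group difference in marginal means at that visit, so it makes no use of the baseline score to reduce residual variance.

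The power calculation describes the first hurdle only. No power is given for either visit. If power for the visit-specific statement is well below 0.90, a trial of a program that works as assumed could end without a significant difference at the visit of interest. It could even end with a significant interaction and no significant difference at either visit.

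**Working it through.** **Inputs.** From Sample Size Calculation: f = 0.15, α = 0.05, ρ = 0.5, ε = 1, k = 2 groups, m = 3 measurements, N = 96 before attrition (48 per arm), 120 after (60 per arm). From Outcome Analysis and Longitudinal Modeling: the model, the gate, and correction by an unnamed method. Assumed here: Bonferroni over T1 and T2 (2.5% each, two-sided) and the pattern of effect over time.

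**1. The plan's own figure.** For the within-between interaction in G*Power:

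- λ = f²·N·m/(1 − ρ) = 0.0225 × 96 × 3/0.5 = 12.96
- df = (k − 1)(m − 1) = 2 and (N − k)(m − 1) = 188
- Power = 0.902 (N = 94 gives 0.896), so 96 is the minimum
- 96/(1 − 0.20) = 120

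The figure reproduces. The between-groups main effect would need N = 314, so it is not the source. The test of time alone gives the same 96 with two groups, but it is not a test of treatment.

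**2. What f = 0.15 means at a visit.** With group differences (0, d, d) in SD units, the deviations from their mean are (−2d/3, d/3, d/3), with sum of squares 2d²/3. Dividing by 12 (each difference splits into ± half, over six cells) gives f² = d²/18, so d = 0.15 × √18 = 0.636 at both visits. For a fading effect (0, d, d/2), f² = d²/24, so d = 0.735 at T1 and 0.367 at T2.

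**3. Power of the planned route.** 20,000 simulated trials per row, compound symmetry, ρ = 0.5: interaction at 5%, then T1 and T2 simple effects from the random-intercept model at 2.5% each.

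| Pattern | Per arm | Gate | T1 | At least one visit | Both |
|---|---|---|---|---|---|
| Sustained | 48 | 0.90 | 0.74 | 0.84 | 0.64 |
| Sustained | 60 | 0.96 | 0.86 | 0.93 | 0.79 |
| Fading | 48 | 0.90 | 0.84 | 0.84 | 0.29 |

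**4. Where the power goes** (T1, sustained effect, 48 per arm):

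- Unadjusted, no gate: 0.87 at 5%, 0.80 at 2.5%
- Unadjusted, behind the gate, at 2.5%: 0.74
- Baseline-adjusted, no gate (residual variance 1 − ρ² = 0.75): 0.945 at 5%, 0.905 at 2.5%

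At the same 2.5%, removing the gate takes T1 from 0.74 to 0.80, and baseline adjustment takes it from 0.80 to about 0.90. The remaining step to 0.945 comes only from giving T1 the full 5%.

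**5. Both visits, baseline-adjusted, no gate.** T1 then T2 in fixed sequence at 5%: T1 0.945, both about 0.90. At 2.5% each: about 0.90 per visit, at least one 0.98, both 0.82.

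**6. Sensitivity to the baseline correlation** (d held at 0.636, 48 per arm). Adjusted T1 at 5% is about 0.94 at ρ = 0.5 and about 0.87 to 0.88 at ρ = 0.2. The planned route also suffers: at ρ = 0.3 the gate falls to 0.77 and gated T1 to 0.65, against 0.89 for adjusted T1.

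**The case against.** The sample size matches the test the protocol names. The mixed model with its interaction is the stated primary inference, and nowhere does the protocol claim 90% power for a single visit. That stands: the 0.90 is correct for what it describes, and a reader who inferred that 96 or 120 is miscalculated would be wrong.

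A reader might also infer that a significant interaction says nothing about whether the program works. The documents do not support this. Randomisation makes the groups equal in expectation at T0, so the interaction null amounts to no group difference at T1 and none at T2. A real interaction therefore implies an effect at some follow-up visit, with its direction read from the estimates. What the interaction leaves open is which visit, and that is what the gated comparisons have to settle.

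The visit-specific figures depend on assumptions. Holm after the gate gives 0.79 at T1 and 0.73 for both. If the gate is used as the intersection test of a closed procedure, each visit can be tested at 5%, giving 0.80 at T1 and 0.87 for at least one. Difference-in-change contrasts from the same model would give 0.79 at T1, 0.90 for at least one visit and 0.69 for both, but the text describes group differences at a time point. Forty-eight per arm is also a floor, because the mixed model keeps partly observed women. These points narrow the gap. None brings T1, or both visits, to 0.90 at the planned attrition.

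The gain from baseline adjustment depends on the baseline correlation, and entry restricted to HDRS-17 scores of 17 to 23 may lower it. That stands, and any restated power should show it. Finally, an omnibus interaction followed by simple effects is a common and valid analysis, and an unseen analysis plan may name the correction. The gate and the model terms, however, are fixed in the protocol itself.

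**Conclusion.** The point holds as a mismatch of power and efficiency; the analysis is not invalid. The stated 0.90 is the power of the 2-df interaction. The route to a claim of benefit at 12 or 26 weeks has power of about 0.74 at T1, 0.84 for at least one visit and 0.64 for both with 48 completers per arm, and 0.86, 0.93 and 0.79 with 60 per arm. These figures rest on f = 0.15 as a sustained effect, ρ = 0.5 and Bonferroni over two visits. A larger family, such as one counting T0 or the within-group contrasts, would lower them.

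A direct baseline-adjusted contrast would do better with the same women and visits. The protocol should change, but the trial is not undermined if it does not. Nor do the documents show that T1 must rank ahead of T2: the primary outcome covers both, and the order is the sponsor's choice.

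**What to change.** - In Outcome Analysis and Longitudinal Modeling, make the primary test the between-group difference in mean HDRS-17 at follow-up, adjusted for baseline (group means constrained equal at T0, or baseline HDRS-17 as a covariate). Remove the significant interaction as a condition for it.
- Prespecify how the two visits share alpha: for example T1 then T2 in fixed sequence at two-sided 5%, or 2.5% at each.
- Treat within-group changes as descriptive.
- In Sample Size Calculation, say that 0.90 refers to the interaction test. Give the power of the chosen contrast with its dependence on the baseline correlation (adjusted T1 at 5%: about 0.94 at ρ = 0.5, about 0.87 to 0.88 at ρ = 0.2).

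The cost is a documented amendment and a registry update, which the Protocol Amendments section already provides for. No extra participants or assessments are needed. With 8 enrolled as of April 2026 and analysis not begun, the change is credible now. The downside is that under the fixed sequence T2 is confirmatory only if T1 succeeds; splitting alpha avoids that but lowers power at each visit to about 0.90 (sustained effect, ρ = 0.5, 48 per arm).

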#### Predictors and Covariate Analysis

Additional analyses will identify baseline predictors of clinical improvement using LMMs and multiple linear regression. To address the dynamic nature of psychological factors, perceived stress (PSS) and menstrual distress (MEDI-Q) will be modeled as time-varying covariates within the LMM framework rather than as static baseline moderators. This allows for the assessment of whether longitudinal fluctuations in these variables are associated with concurrent changes in depressive symptoms. Furthermore, exploratory multilevel mediation analyses may be conducted to examine if changes in PSS or MEDI-Q partially mediate the intervention’s effect on HDRS-17 trajectories.

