#### Procedure

Assessments will be conducted at 3 time points: baseline (T0), postintervention (12 weeks after baseline, T1), and follow-up (26 weeks after baseline, T2).

The baseline assessment will include the collection of sociodemographic and clinical data, the administration of primary and secondary outcome measures, a gynecological consultation to assess hormonal and menstrual health, and the collection of biological samples.

At T1 and T2, follow-up assessments will include the administration of primary and secondary outcome measures as well as biological sample collection.

All psychological assessments will be carried out by a trained professional (psychologist, physician, psychiatrist, or psychiatric nurse), gynecological examinations will be performed by a licensed gynecologist (MD in obstetrics and gynecology), and biological samples will be collected by a registered nurse. Participant timeline, including the schedule of enrollment, interventions, and assessments, is outlined in Table 1. All professionals with direct participant contact—whether via teleconference or in-person—will be women. This decision was reached by consensus within the focus group of women with a lived experience of depression, who expressed that sensitive topics (eg, hormonal changes, gender discrimination, and sexuality in the context of depression) would be better understood by female professionals and that participants would feel more comfortable accordingly.

**Table 1. T1:** SPIRIT (Standard Protocol Items: Recommendations for Interventional Trials) participant timeline.

Study procedure	Trial period					
	Preintervention			Intervention	Postintervention	Follow-up
Time point	–t0	T0	T0	—^a^	T1	T2
Weeks	0	1	2	3‐12	12	26
Enrollment						
Eligibility screen	*✓*					
Informed consent		✓				
Inclusion		✓				
Randomization		✓				
Interventions						
Intervention (3D Program)				✓		
Control group (informational videos)				✓		
Screening assessments						
Sociodemographic information		✓				
Medical and psychiatric history		✓				
Gynecological visit			✓			
Primary outcome						
HDRS-17^b^		✓			✓	✓
Secondary outcomes						
WHODAS 2.0^c^		✓			✓	✓
EQ-5D-5L^d^		✓			✓	✓
PSS^e^** **		✓			✓	✓
MEDI-Q^f^** **		✓			✓	✓
Biological samples						
Plasma			✓		✓	✓
Saliva			✓		✓	✓
Urine			✓		✓	✓
Nails			✓		✓	✓
Hair			✓		✓	✓

a Not applicable.

b HDRS-17: 17-item Hamilton Depression Rating Scale.

c WHODAS 2.0: World Health Organization Disability Assessment Schedule 2.0 (36-item version).

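### The time-varying PSS and MEDI-Q models are said to assess longitudinal fluctuation, but no separation of within-woman from between-woman association is specified

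*Protocol article*

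**What the plan says.** The efficacy model is fixed in the protocol article under Outcome Analysis and Longitudinal Modeling: "These models will include fixed effects for group, time, and their interaction, with a random intercept for participants". PSS and MEDI-Q are not in it.

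The next section, Predictors and Covariate Analysis, describes additional analyses. There, "perceived stress (PSS) and menstrual distress (MEDI-Q) will be modeled as time-varying covariates within the LMM framework rather than as static baseline moderators". The article then draws the inference: "This allows for the assessment of whether longitudinal fluctuations in these variables are associated with concurrent changes in depressive symptoms". It adds that "exploratory multilevel mediation analyses may be conducted to examine if changes in PSS or MEDI-Q partially mediate" the effect of the intervention on HDRS-17.

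PSS, MEDI-Q and HDRS-17 are all measured at baseline, week 12 and week 26 (Procedure and Table 1). The article does not say whether the covariates enter as observed or are centred on each woman's mean, and it mentions no person-mean term.

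**The concern.** A statement about fluctuations going with concurrent changes concerns the same woman at different visits: when her stress is above her own usual level, is her HDRS-17 higher too? A time-varying covariate carries two kinds of variation, stable differences between women and movement within a woman. In a random-intercept model, one slope for the uncentred score uses both. The random intercept handles correlation among a woman's repeated measures; it does not remove the between-woman part of the covariate from the slope.

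Women who are generally more stressed may well be generally more depressed. In that case the uncentred slope can be clearly positive although visit-to-visit movement in stress tells nothing about visit-to-visit movement in depression. The trial could then report that changes in stress or menstrual distress track changes in depression on the strength of stable differences alone. If the optional mediation analysis used the same uncentred terms, it would inherit the problem.

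**Working it through.** **The plan's own figures.** The article gives no figure for this analysis. Its only related calculation is the sample size, where "the minimum sample size estimated was at 96 patients". With f = 0.15, N = 96, m = 3 visits and correlation 0.5, the noncentrality is 0.15² × 96 × 3 / (1 − 0.5) = 12.96 on 2 and 188 degrees of freedom. Power is 0.902 (0.896 at N = 94), and 96 / (1 − 0.20) = 120. Both figures reproduce, and neither bears on this point.

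**Weight on the between-woman slope.** Let the covariate have intraclass correlation (ICC) ρx and the residual ρr, both on a unit-variance scale, with m = 3.

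- Between information: Sb = m[ρx + (1 − ρx)/m] / [(1 − ρr) + mρr]
- Within information: Sw = (m − 1)(1 − ρx) / (1 − ρr)
- Weight w = Sb / (Sb + Sw)
- Bias of the uncentred slope as a within-woman slope = w × (between slope − within slope)

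The ICCs are assumptions, so a range is shown:

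- ρx = 0.3, ρr = 0.7: Sb = 0.67, Sw = 4.67, w = 0.13
- ρx = 0.5, ρr = 0.5: Sb = 1, Sw = 2, w = 0.33
- ρx = 0.8, ρr = 0.2: Sb = 1.86, Sw = 0.50, w = 0.79

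**Simulation on the standardised scale** (96 women, 3 visits, 300 runs per setting, both ICCs 0.5):

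| True within | True between | Uncentred slope (significant) | Deviation term (significant) |
|---|---|---|---|
| 0 | 0.5 | 0.15 (70%) | 0.00 (4.7%) |
| 0 | 0.3 | 0.10 (37%) | 0.00 (3.7%) |
| 0.2 | 0.6 | 0.33 (100%) | 0.20 (77%) |
| 0.3 | 0.3 | 0.30 (100%) | 0.30 (98%) |

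The last row shows that the bias vanishes when the two slopes are equal.

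**On a PSS and HDRS-17 scale.** All inputs are assumed: PSS SD 6 between and 4 within women, random-intercept SD 3, residual SD 3.5, true within slope 0. For a between slope of 0.6:

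- variance of a woman's observed mean PSS: 36 + 16/3 = 41.33
- slope on that observed mean: 0.6 × 36/41.33 = 0.523
- intercept variance given that mean: 9 + 0.36 × 36 × (1 − 36/41.33) = 10.67
- Sb = 3 × 41.33 / (12.25 + 3 × 10.67) = 2.80; Sw = 2 × 16/12.25 = 2.61; w = 0.517
- uncentred slope ≈ 0.517 × 0.523 = 0.27

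The same steps for a between slope of 0.3 give 0.14. Simulation at n = 120, without and with the HDRS-17 entry range of 17 to 23 imposed at baseline, gives:

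| Between slope | No entry restriction | Entry restriction |
|---|---|---|
| 0.6 | 0.26 | 0.13 |
| 0.3 | 0.13 | 0.09 |

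Across these four settings the uncentred slope was significant in 85% to 100% of runs and the deviation term in 0% to 10%. These rates carry simulation error of several percentage points.

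**The case against.** The strongest reply is that nothing in the article says the scores go in raw. It mentions an analysis plan developed with two biostatisticians, which is not shown, and the coding of a covariate in an additional analysis is the kind of detail an article leaves to such a plan. This stands in part: the point must be conditional on uncentred entry. It does not dispose of the point, because the article goes beyond silence. It states that entering the scores as time-varying covariates is what allows the fluctuation question to be answered, and in the model described that does not follow.

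A second reply concerns size. Eligibility limits baseline HDRS-17 to 17 to 23, so its baseline SD cannot exceed about 3, and a simulation without that limit overstates the bias. This stands. With a between slope of 0.6 the restriction cuts the slope from 0.26 to 0.13. Bias remains, but the restricted figures are the relevant ones for this trial.

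A reader might infer more from the section, and the article does not support these readings:

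- *The treatment effect will be distorted by adjusting for post-randomization variables.* The efficacy model is set out separately without these covariates, and nowhere is the treatment effect to be read from the covariate model.
- *Baseline prediction has been abandoned.* Baseline predictors remain an aim, and a reason is given for treating these two scores differently.
- *The mediation analysis has no time order.* It is optional and exploratory, and the article does not fix mediator and outcome at the same visit. A lagged version adjusting for week-12 HDRS-17 would answer a different question.
- *Women who do not menstruate will drop out of the MEDI-Q model.* Transgender women are eligible, so the question is fair, but no scoring or deletion rule is stated and it is a separate matter.

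**Conclusion.** The concern holds in a conditional and limited form. The stated interpretation is about within-woman change, and the described model secures it only if within- and between-woman variation are separated, which the article does not specify. With uncentred scores, 120 women and no true within-woman association, the slope would be about 0.09 to 0.13 HDRS-17 points per PSS point under the entry restriction (0.13 to 0.26 without it), for between slopes of 0.3 to 0.6, and would usually be significant. Every variance and slope behind these figures is assumed.

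To say that the model cannot support the claim would be too strong: the mixed slope equals the within-woman slope when the two associations agree, and the same LMM framework supports the claim once the covariate is split. The article gives no reason to expect that agreement.

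The consequence is confined to an additional analysis, and to the optional mediation analysis if it reuses the same terms. The primary group-by-time test and the sample size are unaffected. It is worth correcting, but it does not threaten the trial's main conclusion.

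**What to change.** Specify in the analysis plan that PSS and MEDI-Q each enter the covariate model as two terms: the woman's own mean over her visits, and the deviation of each visit from that mean. State that any claim about fluctuations rests on the deviation term alone, and that the mean term describes differences between women. State also that the model under Outcome Analysis and Longitudinal Modeling, without these covariates, is the sole source of the treatment effect. If the unseen analysis plan already does this, only the sentence in the article needs qualifying.

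The cost is two derived variables per covariate, a few lines of text, and a slightly less precise slope, because between-woman information no longer feeds into it. No new data are needed. The Results section reports that data analysis has not commenced, so this can still be prespecified.
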